## Abstract

**Background:**

Amnestic mild cognitive impairment (aMCI), the predominant subtype of mild cognitive impairment, carries the highest risk of progression to Alzheimer disease among all mild cognitive impairment subtypes. Currently, clinical practice lacks an established, authoritative treatment method for this condition. Prior clinical evidence indicates acupuncture may enhance cognitive function in individuals with mild cognitive impairment. Further clinical evidence suggests Gold Needle therapy demonstrates significant therapeutic effects for challenging and refractory conditions; however, a critical gap exists: no clinical trials currently ascertain whether Gold Needle therapy surpasses conventional acupuncture in treating aMCI. This trial aims to rigorously evaluate the therapeutic efficacy and safety of the Gold Needle “Regulating Spirit” method for clinical symptoms in patients with aMCI, alongside investigating its underlying imaging and biochemical mechanisms.

**Objective:**

This proposed study aims to identify imaging and laboratory biomarkers for the early diagnosis of aMCI, thereby providing a theoretical foundation for clinical practice.

**Methods:**

This randomized controlled trial will recruit 90 patients diagnosed with aMCI from the Beijing Hospital of Traditional Chinese Medicine, affiliated with Capital Medical University, alongside 20 healthy volunteers. The 90 patients with aMCI will be randomly allocated to 1 of 3 groups: the Gold Needle “Regulating Spirit” group uses gold-based needles, the general acupuncture “Regulating Spirit” group, or a sham acupuncture control group. The Gold Needle “Regulate Spirit” group uses gold-based needles, the general acupuncture “Regulate Spirit” group uses standard needles, and the sham acupuncture group administers Park needles. Participants will undergo 3 sessions per week of their assigned acupuncture or placebo treatment over a continuous 12-week period.

**Results:**

This study was initiated on September 1, 2023. As of October 30, 2025, 110 eligible participants had been enrolled, and data collection had been completed in full. Data analysis is currently underway, and the preliminary results are expected to be available by June 2025. We hypothesize that, compared with the filiform needle-based mind-regulating acupuncture group, the golden needle-based mind-regulating acupuncture group will demonstrate superior efficacy in improving cognitive impairment. This superiority will be reflected in multiple key outcome measures, including Montreal Cognitive Assessment and Mini-Mental State Examination scores, plasma biomarkers, and functional magnetic resonance imaging findings.

**Conclusions:**

We anticipate that by the end of the trial, we will be able to definitively ascertain whether the gold acupuncture needle technique for “regulating spirit” offers a significant advantage in treating aMCI, and further investigate the nature of this therapeutic benefit, to offer a more efficacious intervention for the clinical management of aMCI and the prevention of Alzheimer disease.

## Introduction

Mild cognitive impairment (MCI) is characterized as an intermediary condition between normal aging and Alzheimer disease (AD), wherein individuals experience memory deficits that exceed the normative expectations for their age, alongside varying degrees of impairments in other cognitive functions; however, these symptoms do not significantly disrupt daily living activities [1]. Recent epidemiological research suggests that the estimated overall prevalence of MCI in China is approximately 15.5% [2]. As the aging population in China continues to expand, there has been a significant rise in the prevalence of MCI. MCI encompasses several subtypes, with the most prevalent being amnestic mild cognitive impairment (aMCI) [3]. Distinct from other subtypes, aMCI is primarily characterized by a significant decline in memory function [4], which serves as its principal clinical manifestation. This feature renders it more closely associated with AD and makes it the subtype most susceptible to conversion into AD [5]. A study conducted among a random sample of 3246 older Chinese community members revealed that the prevalence of aMCI was 17.1%, with an annual incidence rate of 70.57%. Furthermore, the conversion rate from aMCI to AD in the absence of intervention ranged between 10% and 17% [6]. The most salient manifestations of AD include significant memory deficits, alongside cognitive deterioration, visual-spatial dysfunction, executive function impairment, and neuropsychiatric symptoms that are independent of cognitive processes [7]. These symptoms collectively contribute to a deterioration in the capacity for independent living and a significant impairment of self-care abilities, thereby profoundly impacting the quality of life as well as the physical and mental health of older adults. aMCI is regarded as a preliminary phase of AD, and identifying effective treatment strategies for aMCI holds significant clinical implications for the prevention of AD.

At present, the management of aMCI predominantly relies on pharmacological interventions, with the medications used frequently mirroring those used in AD treatment strategies, including donepezil, memantine, and cholinesterase inhibitors [8,9]. Nevertheless, research has demonstrated that these medications not only fail to impede the progression of aMCI to AD but also induce adverse effects during their administration [10]. Therefore, there exists an urgent clinical demand for a safer alternative treatment with reduced side effects for individuals diagnosed with aMCI. Acupuncture is a traditional Chinese medical practice and one of the primary modalities for disease treatment within traditional Chinese medicine. It is considered safe, exhibits minimal side effects, and demonstrates significant long-term efficacy. Acupuncture has demonstrated potential efficacy in ameliorating mild cognitive impairment and enhancing memory, positioning it as a viable complementary and alternative therapy [11,12]. Our prior animal studies have demonstrated that acupuncture can enhance memory and alleviate cognitive impairments in AD mouse models, thereby offering a substantial experimental foundation [13,14]. Gold Needles, primarily composed of gold, are used in acupuncture treatments due to their advantageous properties. In comparison to other metallic materials, gold exhibits more stable chemical characteristics and a softer texture, facilitating precise control over penetration direction while minimizing discomfort for patients [15]. In clinical practice, the therapeutic efficacy of Gold Needles for a range of conditions, including neurological disorders, surpasses that of conventional metal needles [15]. Currently, there is a paucity of high-quality clinical trials investigating acupuncture treatment for aMCI, and no clinical studies have been conducted on Gold Needle intervention for this condition. Therefore, it is imperative to undertake relevant clinical investigations. The onset of aMCI is insidious, and certain symptoms may not be readily apparent, rendering them susceptible to oversight. As an early manifestation of AD, aMCI exhibits numerous similarities with AD [16]. The precise mechanisms underlying the development of aMCI remain unclear, and numerous hypotheses have been proposed to elucidate this phenomenon. aMCI is predominantly characterized by the development of senile plaques formed from beta-amyloid (Aβ) protein deposits, alongside the accumulation of tau-related proteins that give rise to neurofibrillary tangles [17].

In light of the clinical symptoms and pathological characteristics associated with aMCI, this trial incorporates a comprehensive approach that includes neuropsychological assessments, cognitive function evaluations, imaging analyses, and molecular biological investigations to assess the efficacy and safety of the Gold Needle “regulating the spirit” method in treating aMCI.

## Methods

### Study Design

This study is designed as a randomized controlled trial (RCT) using block randomization. We will recruit 90 participants diagnosed with aMCI and allocate them into 3 groups in a 1:1:1 ratio; specifically, the Gold Needle “Regulating Spirit” group, the general acupuncture “Regulating Spirit” group, and a sham acupuncture control group. Additionally, we will include 20 healthy volunteers to serve as a control group. The participants’ gender, age, and educational background will be aligned with those of the patients with aMCI. A total of 90 patients with aMCI will undergo treatment for 12 weeks in groups, receiving interventions 3 times per week. Data collection for all enrolled individuals will occur at baseline (week 0), week 12, and week 24.

The study protocol has been registered in ClinicalTrials [18]. The flowchart of the trial is shown in Figure 1 and the research content at different periods of the trial is given in Table 1.

**Figure 1. F1:**
[figure not shown]
Flowchart diagram. aMCI: amnestic mild cognitive impairment; DTI: diffusion tensor imaging; FAQ: Functional Activities Questionnaire; HAMA: Hamilton Anxiety Scale; HAMD: Hamilton Depression Scale; 3D-MRI: 3D–magnetic resonance imaging; Aβ: beta-amyloid; MoCA: Montreal Cognitive Assessment; NfL: neurofilament light chain; rs-fMRI: resting-state functional magnetic resonance imaging; TS: Tiao shen (English: “Regulating Spirit”).

**Table 1. T1:** Research content during different periods of the trial.

	Enrolment	Baseline	Intervention period (12 wk, 3 times per week)				Follow-up
Week	−1	0	1-4	5-8	9-11	12	24
Inclusion criteria	✓						
Exclusion criteria	✓						
Randomization	✓						
Informed consent	✓						
Intervention							
Gold Needle–TS^a^ acupuncture			✓	✓	✓	✓	
TS-acupuncture			✓	✓	✓	✓	
Shame acupuncture			✓	✓	✓	✓	
Assessment							
Demographic data		✓					
MoCA^b^		✓				✓	✓
FAQ^c^		✓				✓	✓
HAMA^d^		✓				✓	✓
HAMD^e^		✓				✓	✓
3D-MRI^f^		✓				✓	
rs-fMRI^g^		✓				✓	
DTI^h^		✓				✓	
Aβ^i^_42_/Aβ_40_		✓				✓	
NfL^j^		✓				✓	
P-tua181		✓				✓	
P-tua217		✓				✓	
Adverse events			✓	✓	✓	✓	
Reasons for dropout			✓	✓	✓	✓	
Withdrawals			✓	✓	✓	✓	

a TS: Tiao shen (English: “Regulating Spirit”).

b MoCA: Montreal Cognitive Assessment.

c FAQ: Functional Activities Questionnaire.

d HAMA: Hamilton Anxiety Scale.

e HAMD: Hamilton Depression Scale.

f 3D-MRI: 3D–magnetic resonance imaging.

g rs-fMRI: resting-state functional magnetic resonance imaging.

h DTI: diffusion tensor imaging.

i Aβ: beta-amyloid

j NfL: neurofilament light chain.

### Recruitment and Study Population

This study used a prospective, RCT design. Individuals with memory impairment were recruited through hospital referrals, poster advertisements, and community screenings conducted by collaborating organizations. Initial screenings identified individuals who met the inclusion criteria for the study’s aMCI cohort. All participants provided voluntary written informed consent prior to the commencement of the study.

### Eligibility

#### Diagnostic Criteria

In accordance with the diagnostic criteria for aMCI established in 2004, participants were required to meet the following criteria: (1) memory impairment as the chief complaint, confirmed by a knowledgeable person; (2) objective evidence of memory impairment, with the observed decline in memory not proportional to age-related expectations; (3) other general cognitive functions essentially normal; (4) cognitive impairment insufficient to warrant a diagnosis of dementia and evaluated in relation to the individual’s prior performance, without notable deficits in social or occupational functioning; and (5) preserved functional independence, with fundamental daily living skills maintained within normal limits.

#### Inclusion Criteria

The inclusion criteria for patients with aMCI were as follows: (1) meeting the diagnostic criteria for aMCI; (2) the initial episode of illness is characterized by a history of memory impairment lasting at least 3 months, with no prior indications of other neurological or psychiatric disorders; (3) Clinical Dementia Rating score of 0.5 points; (4) individuals aged between 50 and 75 years, with no gender restrictions; (5) the minimum educational duration is 1 year or more; and (6) participation was voluntary, and informed consent was obtained from the person participating.

The inclusion criteria for healthy volunteers are as follows. First, the age should be between 50 and 75 years (male or female). Second, there should be no documented history of abnormalities related to the heart, liver, kidneys, digestive tract, nervous system, psychological conditions, and metabolic disorders. A thorough physical examination should reveal normal findings in electrocardiogram readings, blood pressure, heart rate, respiratory function, and pertinent laboratory tests. Finally, there should be no linguistic or cognitive barriers, allowing for straightforward completion of the questionnaire.

#### Exclusion Criteria

Exclusion criteria for patients with aMCI are as follows: (1) a history of prior intracranial hemorrhage or ischemic disease accompanied by neurological localizing signs, along with imaging findings indicative of cerebral small vessel disease (Fazekas score ≥2 points); (2) individuals experiencing various neurological disorders that may lead to brain dysfunction, including but not limited to epilepsy, depression, brain tumors, Parkinson disease, metabolic disorders, encephalitis, multiple sclerosis, head trauma, and normal pressure hydrocephalus; (3) cognitive impairment associated with various systemic diseases, including liver dysfunction, renal dysfunction, thyroid disorders, severe anemia, deficiencies in folic acid and vitamin B_12_, carbon monoxide poisoning, specific infections (such as syphilis and HIV/AIDS), as well as substance use involving alcohol and drugs; (4) a delay in mental and neurological development; (5) certain contraindications for nuclear magnetic resonance examinations; (6) a disease that makes it impossible for a person to complete cognitive tests; (7) within 1 month of initiating treatment with antidementia pharmacological agents; and (8) the participants declined to provide written, informed consent for their involvement in the study.

Exclusion criteria for healthy volunteers are as follows: (1) a well-documented history of disorders affecting the central nervous system, cardiovascular system, respiratory system, kidneys, liver, digestive tract, or other diseases and physiological conditions that may potentially confound test results is evident; (2) consumption of any prescription or over-the-counter medication within 2 weeks prior to the commencement of the experiment; and (3) severe acute or chronic organic and mental health disorders.

### Randomization, Allocation Concealment, and Blinding

This study used a block-randomized design, wherein an independent statistician—who was not involved in trial assessment, treatment allocation, or statistical analysis—generated the randomization sequence using SAS 9.2 (SAS Institute) software’s PROC PLAN (with a block length of 6). An independent research assistant ensured allocation concealment through the use of opaque, sealed envelopes. In this study, the acupuncturist, outcome evaluator, and data analyst were assigned by different individuals to ensure objectivity; both patients and evaluators remained blinded throughout the process. Given the unique nature of Gold Needle manipulation, challenges arose in establishing acupoint settings for the sham group and in maintaining blinding for the acupuncturist. To address these issues, we strictly adhered to patient blinding protocols and scheduled individual appointments at staggered times.

### Intervention

#### Gold Needle “Regulating Spirit” Group

The patients in this study underwent Gold Needle “Regulating Spirit” therapy, which included acupuncture sessions administered three times per week over a duration of 12 weeks. The acupoint locations follow the 2006 version of *Names and Locations of Acupoints* (GB/T12346-2006) and the operational techniques are in accordance with the national standard textbook of *Moxibustion and Acupuncture Techniques*. The selected acupoints include Baihui (GV20), Sishencong (EX-HN1), Shenting (GV24), Benshen (GB13), Yintang (GV29), Renzhong (GV26), Shenmen (HT7), Feishu (BL13), Xinshu (BL15), Ganshu (BL18), Pishu (BL20), Shenshu (BL23), and Geshu (BL17; the locations are presented in the following table). The patient is positioned in laterally exposing the head, back, and wrist areas. Disposable Huatuo brand sterile gold needles 0.30×40 mm. The acupuncture points and the practitioner’s hands are thoroughly disinfected with 75% alcohol. All acupoints on the head are needled at an angle of 15‐30° to a depth of 1 inch, while those on the back of the body are needled at the same angle and depth but directed upward. At GV26, the needle is inserted 0.3 cun upward, while direct insertion at GV29 and HT7 is performed at a depth of 0.3 cun. After obtaining the “Qi,” each acupuncture point is needled for 30 seconds. Using a technique of balanced supplementation and drainage, the needle is retained in situ for 30 minutes until the patient experiences a moderate sensation of soreness or fullness in the affected region. The locations of each acupuncture point are listed in Table 2.

**Table 2. T2:** The acupuncture points and their locations.

Acupoints	Locations
Baihui (GV20)	At the top of the head, 5 cun directly above the anterior hairline. In the depression midway between the anterior and posterior hairline, 1 cun anterior to the midpoint.
Sishencong (EX-HN1)	On the vertex, 1 cun from the front, back, left, and right to GV20, common 4 points
Shenting (GV24)	At the head, 0.5 cun straight up from the midpoint of the front hairline.
Benshen (GB13)	Located at the superior aspect, 0.5 cun above the anterior hairline and 3 cun lateral to the midline of the cranium.
Yintang (GV29)	At the forehead, at the midpoint between the two medial ends of the eyebrow.
Renzhong (GV26)	In the face, at the point where the upper 1/3 of the philtrum meets the middle 1/3.
Shenmen (HT7)	In the anterior region of the forearm, at the distal lateral aspect of the ulnar side of the palmar flexor tendon, adjacent to the radial side of the wrist.
Feishu (BL13)	In the spinal area, 1.5 cun lateral to the midline at the third thoracic spinous process.
Xinshu (BL15)	In the spinal area, at the level of the 5th thoracic vertebra, 1.5 cun lateral to the midline posterior.
Ganshu (BL18)	In the spinal area, at the level of the 9th thoracic vertebra, 1.5 cun lateral to the midline posteriorly.
Pishu (BL20)	In the spinal region, at the level of the 11th thoracic vertebra, 1.5 cun lateral to the midline posteriorly.
Shenshu (BL23)	In the spinal area, 1.5 cun lateral to the midline at the level of the second lumbar spinous process.
Geshu (BL17)	In the spinal area, 1.5 cun lateral to the midline at the 7th thoracic spinous process.

#### The General Acupuncture “Regulating Spirit” Group

These patients received moxibustion therapy using general needles to regulate the spirit, with acupuncture sessions conducted three times a week for a total of 12 weeks. The acupoint locations adhere to the standards established by the World Health Organization (WHO) in 2008, while the operational techniques are based on the national standard textbook titled *Acupuncture and Moxibustion*. The selection of acupoints aligns with that of the Gold Needle “Regulating Spirit” group. Sterile disposable needles from the Huatuo brand, measuring 0.30×40 mm, are used. Position, technique, and manipulation are the same as those in the Gold Needle group.

#### Sham Acupuncture Group

The needle used is the model 0.30×40 mm Park Comfort Needle. The comfort needle is designed to resemble a conventional needle, featuring a collapsible blunt tip. Upon contact with the skin, this blunt tip automatically retracts into the hollow shaft of the needle, preventing any penetration. Acupuncture point manipulation: Feishu (BL13), Xinshu (BL15), Ganshu (BL18), Pishu (BL20), Shenshu (BL23), and Geshu (BL17). Park comfortably administered acupuncture treatments by selecting only back acupoints, strictly adhering to the blinding of patients, and scheduling individual appointments at different times.

#### Normal Group

Participants in the normal group did not require any treatment.

### Outcome Assessment

The variables examined in this study encompass both demographic and clinical characteristics, as well as the primary and secondary outcome measures. The fundamental characteristics of each group were assessed at baseline (wk 0). The primary and secondary outcome measures were evaluated at baseline, at the conclusion of the intervention (wk 12), and again at 24 weeks post follow-up.

### Basic Characteristics

Recruiters will use a self-constructed questionnaire to collect demographic information from participants, including gender, age, educational attainment, marital status, living arrangements, occupation, and socioeconomic status, along with their medical history and substance use.

### Primary Outcomes

The Montreal Cognitive Assessment (MoCA) was used to assess the patients’ overall cognitive function [19]. MoCA encompasses several cognitive domains, including Visuospatial or Executive Function, Attention and Calculation, Naming, Delayed Recall, Orientation, Language, and Abstract Reasoning. The total score ranges from 0 to 30 points, with higher scores indicating superior functionality.

### Secondary Outcomes

Neuropsychiatric symptoms and a decline in functional abilities are significant concomitant manifestations of AD, with their emergence serving as an indicator that aMCI is progressing toward AD [20]. Consequently, this study incorporated the Functional Activities Questionnaire, along with the Hamilton Anxiety Scale and the Hamilton Depression Scale [21,22].

### Other Indicators

Acquire multimodal magnetic resonance imaging (MRI) data, including 3D-MRI, resting-state functional MRI, and diffusion tensor imaging, to construct networks related to cognitive function and brain structure [23]. The study participants, who underwent imaging, were scanned using a Siemens Novus 3.0T MRI system, which was manufactured in Germany.

Using single-molecule immunoarray technology for the detection of biomarkers in plasma, we assess the intervention level of the gold standard concerning the Aβ42/Aβ40 ratio in peripheral plasma, alongside measurements of plasma neurofilament light chain, plasma P-tau181, and plasma P-tau217 [24,25].

### Safety Measurement

Throughout the study, the acupuncturist systematically monitored, documented, and communicated adverse events (AEs) using open-ended inquiries. Within 24 hours of the AE occurrence, it was categorized as either treatment-related—common examples being subcutaneous hematoma, persistent pain postneedling, and syncope—or treatment-unrelated. Follow-up continued until the AE was adequately resolved.

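### Adverse events are elicited and recorded by the acupuncturist, who knows the arm, and the assessor of relatedness is not named, so any by-arm safety statement is open to observer bias

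*Protocol article*

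**What the plan says.** The Safety Measurement section of the protocol article states that "the acupuncturist systematically monitored, documented, and communicated adverse events (AEs) using open-ended inquiries". It continues: "Within 24 hours of the AE occurrence, it was categorized as either treatment-related" or as unrelated. That sentence is passive and names no assessor. The examples of related events are hematoma, pain that persists after needling, and syncope.

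The section on randomization, concealment and blinding says that "the acupuncturist, outcome evaluator, and data analyst were assigned by different individuals to ensure objectivity" and that "both patients and evaluators remained blinded throughout the process". It also concedes that "challenges arose in establishing acupoint settings for the sham group and in maintaining blinding for the acupuncturist". The remedy it gives is patient blinding and staggered appointments, neither of which blinds the operator.

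The Abstract and the end of the Introduction both name safety, beside efficacy, as something the trial will evaluate. The Introduction also credits gold needles with "facilitating precise control over penetration direction while minimizing discomfort for patients".

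**The concern.** The design separates the person who treats from the person who assesses, in order to protect objectivity, and keeps the assessor blinded. That protection is described for outcome evaluation. Safety ascertainment goes to the treating role instead.

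Open-ended questioning depends on the questioner: how it is asked, whether it is followed up, and whether the answer is judged worth recording. If the questioner knows the arm and expects one needle to be gentler, the count of recorded events can differ between arms without a true difference, or a true difference can be hidden. At stake is the trial's ability to say anything comparative about the safety of gold versus general needles, or of needling versus sham. The primary outcome, the MoCA, is not affected by this point.

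**Working it through.** No formula applies: the point concerns who ascertains events and what that person knows. The check sets the sections side by side.

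1. **Who asks and records?** The acupuncturist (Safety Measurement). This is stated outright. No other role is given a safety task anywhere in the article.

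2. **Does that person know the arm?** The article does not say in so many words that the acupuncturist was unblinded, but it follows.
   - Only patients and evaluators are listed as blinded, and blinding the acupuncturist is acknowledged as a difficulty.
   - Gold versus general: the operator works with needles of a different material, which the Introduction describes as softer.
   - Active versus sham: in the Park needle "this blunt tip automatically retracts into the hollow shaft of the needle, preventing any penetration", and the sham is given by "selecting only back acupoints". That is 6 named points, against 13 named points on head, face, wrist and back in both active arms.

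3. **Who judges relatedness?** Not stated. The passive sentence directly follows the one about the acupuncturist and no other role appears, so the acupuncturist is the likely reading and no more than that.

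4. **Is a blinded person available?** Yes, the outcome evaluator. Table 1 places clinical assessments at weeks 0, 12 and 24, so there are two visits after the start of treatment at which an evaluator sees the patient. The acupuncturist sees the patient at 3 × 12 = 36 sessions.

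5. **Does expectation have a direction?** The Introduction expects less discomfort with gold needles. Of the three example events, lasting pain is subjective; hematoma and syncope are fairly objective.

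6. **Can the bias be sized?** No. The article gives neither an adverse-event rate nor a rate of under-recording. Suppose both needle arms have the same true proportion p, and a fraction u of gold-arm events goes unrecorded. The apparent risk ratio is then p(1 − u)/p = 1 − u, whatever p is. With 30 per arm, assumed p of 10%, 20% or 30% gives 3, 6 or 9 patients; an assumed u of one third leaves 2, 4 or 6 in the gold arm, a ratio of 0.67 each time. That result only restates the assumed u. It shows that one to three patients are enough to produce such a ratio; it does not estimate the bias.

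Steps 1 and 2 alone establish the risk in eliciting and recording. Step 3 adds a possible second route, through classification, that the article leaves open.

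**The case against.** The strongest reply is that acupuncturist reporting is unavoidable and partly protected. The acupuncturist is present at every session and best placed to see a faint or a bleed; two assessment visits could only supplement this. Much of the information comes from patients, who are described as blinded, and two of the three example events are fairly objective. All of this stands. It supports keeping in-session reporting by the acupuncturist and limits the severity, but it does not make the questioning or the recording blind.

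Several stronger readings are tempting and are not supported:

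- **That the acupuncturist judges relatedness.** The article does not say so, and a full protocol may name the assessor.
- **That a biased between-arm test is planned.** No such test is described. Adverse events are not among the listed primary, secondary or other outcomes, the Statistical Analysis section does not mention them, and the stated superiority hypothesis concerns efficacy only. The point is about the data behind any by-arm safety statement that is eventually made.
- **That the soreness sought during treatment blurs into an adverse event and favors gold.** The intended sensation belongs to needle retention, whereas the example event is pain that persists afterwards. The general group section also gives both needle arms the same position, technique and manipulation.
- **That calling a sham-arm bruise unrelated would be bias.** With a non-penetrating needle it may be a correct causal judgement.
- **That a ratio near 0.67 is to be expected.** It follows by construction from an unsourced one-third loss. Moreover, 2 vs 3, 4 vs 6 and 6 vs 9 of 30 give two-sided Fisher p-values of 1.00, 0.73 and 0.55, so differences of that size could not be told from chance whoever recorded them.

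**Conclusion.** The concern holds in a limited form. Adverse events are elicited and recorded by someone who knows the arm, while a blinded evaluator exists and has no described safety role. Because safety is a stated aim and the assignment is written into the article, this is a design choice and not a detail left to another document. Any by-arm safety statement is open to observer bias, most of all for subjective events. Neither the size of the bias nor its actual direction can be derived from the document; only the direction of the expectation is on record.

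The conclusion rests on one inference, that the operator can tell the needles and point sets apart, which the article's own description makes hard to doubt. It does not depend on who classified relatedness. It is worth correcting in analysis and reporting, and it does not undermine the efficacy results.

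**What to change.** The Results section says that data collection is complete, so the questioning cannot be redone. What can still be done:

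1. Base any by-arm safety comparison on all recorded adverse events regardless of relatedness, with the treatment-related subset as secondary. This removes the classification step from the main comparison.
2. Have the existing blinded evaluator classify relatedness from the event records with arm and needle type masked, and report this beside the classification made at the time. Name who made the latter.
3. Whether or not step 2 is done, state in Safety Measurement that elicitation and recording were unblinded, and make no firm comparative safety claim between arms.
4. In the follow-on trial, keep acupuncturist reporting of in-session events, and have the blinded evaluator also ask a standard adverse-event question at the existing assessment visits.

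**Cost.** No new staff or visits: some hours of masked classification, a few sentences of text, and one added question per assessment visit in the next trial. **Downside.** The masked assessor has less bedside context. An event described at the head or wrist may hint at an active arm, although it cannot separate gold from general because those arms share the same points. Masked classification cannot recover events that were never elicited or recorded, which is why step 3 applies in every case.
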